## Abstract

**Background::**

As one of the most challenging complications in the management of diabetes mellitus, painful diabetic peripheral neuropathy (PDPN) is accompanied by various clinical manifestations, including numbness, burning, coldness, and other sensory abnormalities in the extremities. Meanwhile, PDPN seriously affects the life quality of patients and causes great pain. Western medicine mostly provides symptomatic treatments, such as antioxidants, aldose reductase inhibitors, nerve nutrition, microcirculation improvement, and analgesic drugs on the basis of blood sugar control. Although certain efficacy has been achieved, the problem has not been solved at root. Mudan granules have some advantages in the treatment of PDPN, but there is insufficient high-quality clinical studies to verify this. Therefore, the purpose of this study was to evaluate the efficacy and safety of Mudan granules in treating PDPN.

**Methods::**

A randomized, double-blind, placebo, and parallel-controlled trial design was used to study the efficacy and safety of Mudan granules in the treatment of PDPN. In this study, 93 patients with painful diabetic neuropathy were recruited and randomly divided into a treatment group and a placebo group based on 1:1. The treatment group was given Mudan granules and the control group accepted placebo treatment, and the basic treatment was performed according to the recommended guidelines. During the treatment period, the patients’ visual analog scores, clinical efficacy, Medical Outcomes Study 36-item Short-Form Health Survey (SF-36) scores, nerve conduction velocity, and drug-induced adverse reactions were observed at baseline after 8 and 10 weeks.

**Discussion::**

This study will evaluate the efficacy and safety of Mudan granules in treating PDPN. The experimental results will provide evidence support to treat PDPN with Mudan granules.

**Trial registration::**

DOI 10.17605/OSF.IO/5CE32.

## Introduction

1

Painful diabetic peripheral neuropathy (PDPN) is one of the common chronic complications of diabetes. Symptomatic DPN occurs in 50% of patients with diabetes, and about 15% of patients have symptoms that are quite severe, thus requiring treatment.^[1–3]^ The incidence of PDPN ranges from 10% to 16% depending on the diagnostic criteria.^[1]^ The clinical manifestations include burning, electric shock, acupuncture or blunt pain, more at night, fatigue or excitement when aggravating, often accompanied by hypersensitivity.^[4]^ PDPN patients usually suffer from depression and sleep disorders that seriously affect their daily life and quality of life.^[5,6]^

There is no clinically definitive efficacious treatment, so a comprehensive treatment must be taken. According to western medicine, the treatment of PDPN is based on blood sugar control, while improving microcirculation, aldose reductase inhibitors, antioxidants, ion channel inhibitors, nerve nutrition, tricyclic antidepressants, opioid analgesics, and antiepileptic drugs.^[7]^ However, even with the above mentioned drugs, the pain in PDPN patients still cannot be relieved. Currently, the pain caused by diabetic peripheral neuropathy is one of the world's most difficult problems in the treatment of pain, and there exist limitations in solely relying on modern medical treatments. Therefore, the advantages of traditional Chinese medicine (TCM) can be fully utilized, combined with Western medicine.

In recent years, some studies have revealed that TCM has advantages in treating PDPN with fewer adverse reactions.^[8]^ Mudan granules are composed of radix paeoniae root, *Salvia miltiorrhiza*, *Ligusticum chuanxiong*, red flower, rhizoma corydalis, Sappanwood, *Astragalus membranacea*, *Panax notoginseng*, and caulis spatholobus.^[9]^ Modern studies have proved that Sappanwood, Rhizoma corydophila, caulis spatholobi, *P notoginseng*, and *S miltiorrhiza* all have antioxidant, anti-inflammatory, and vascular protection effects.^[10–14]^ Rhizoma corydalis and *L chuanxiong* have the effects of promoting Qi and activating blood, and removing stasis and relieving pain; caulis spatholobus, Sappanwood, and miltiorrhiza can enhance blood circulation and stasis; *P notoginseng* can help blood circulation and pain; Astragalus is intended to enrich Qi and promote blood circulation, nourish blood, and achieve the effects of removing blood stasis. The combined use of all drugs invigorate Qi and promot blood circulation, and clear collaterals and relieve pain, which suits PDPN pathogenesis of Qi deficiency and blood stasis.

The treatment of PDPN by Mudan granules is clinically effective. It has been proved that Mudan has protective effect on the structure and function of nerve tissue in animal experiments,^[15–17]^ because these conclusions are based on animal experimental studies and control studies of low methodological quality. At present, there is no rigorous randomized controlled trial to investigate the efficacy and safety of Mudan granules in the treatment of PDPN. Therefore, we will evaluate the efficacy and safety of Mudan granules in treatmenting PDPN through this randomized controlled trial.

## Materials and methods

2

### Study design

2.1

This is a randomized, double-blind, and placebo-controlled design. A total of 93 patients with painful diabetic neuropathy recruited in this study will be randomized at the ratio of 1:1 to receive treatment and placebo groups for 8 weeks, and the evaluators will assess and analyze the outcomes at 3 time points (pre-treatment, 8 and 10 weeks). The Jiangxi health vocational college will be responsible for data management and statistics. The flow chart of the trial is shown in Fig. 1.

**Figure 1 F1:**
[figure not shown]
Flow diagram of the trial.

### Ethics and registration

2.2

This research protocol were conducted in accordance with the Declaration of Helsinki and Ethical Guidelines for Clinical Research and approved by our Clinical Research Ethics Committee. The protocol conforms to the Standard Protocol Items: Recommendations for Interventional Trials (SPIRIT) 2013 Statement,^[18]^ and the results were reported on the basis of the Consolidated Standards of Reporting Trials (CONSORT) Statement extension for trials.^[19]^ This experiment has been registered in the open science framework (OSF) (registration number: DOI 10.17605/OSF.IO/5CE32). All patients and their families signed a written informed consent form before the study, and they could discontinue or withdraw from the study at any time during the study.

### Patients

2.3

#### Participant recruitment

2.3.1

The recruitment information will be published on the hospital website, WeChat public website, Facebook, Weibo, and other official platforms to recruit potential patients. The patients who meet the inclusion criteria will have their personal data recorded in detail by the study staff. Moreover, the patients will be replaced by a number and managed by a dedicated person. All information will be stored in a database that can only be accessed by the staff responsible for randomization and blinding.

#### Inclusion criteria

2.3.2

(1)Patients diagnosed with type 2 diabetes according to the criteria of WHO in 1999, aged from 40 to 70;(2)Patients presented with obvious spontaneous neuralgia and numbness and other neuropathic symptoms, which were obvious in both lower limbs, and the pain was like burning knife to cut worms and dragging and needling, often accompanied by aggravation at night and/or sleep disturbance. Most importantly, the symptoms lasted for >6 months;(3)Electromyography showed a decrease in motor sensory nerve conduction velocity (MNCV <45 m s^−1^, SNCY <45m s^−1^);(4)Patients with pain visual analogue score (VAS) >4, without analgesic medication in the last 1 week;(5)Michigan neuropathy screening instrument (MNSI) >2 point.(6)Fasting blood glucose <8 mmol/L; 2 hours postprandial blood glucose <15 mmol/L, glycosylated hemoglobin <8.5%.

#### Exclusion criteria

2.3.3

(1)Combined with other diseases, injuries, or drug taking history that may lead to peripheral neuropathy, such as pernicious anemia, hypothyroidism, and lower extremity vascular diseases (disappearance or weakening of dorsal foot artery fluctuation, varicose veins, etc); history of lower extremity trauma or surgery; drug use history such as vincristine and phenytoin sodium; history of heavy metal poisoning.(2)Presence of abuse of alcohol or drugs, or malnutrition in one recent year.(3)Previous history of cervical and lumbar spondylosis and radiculopathy.(4)Pedal edema.(5)Severe hemorrhagic disease or bleeding tendency.(6)Intolerable to surgery or drugs due to vital organ dysfunction.(7)Poor compliance.(8)Rheumatism and rheumatoid diseases.(9)Participating in other clinical trials.

## Randomization and blinding

3

The random sequence numbering will be obtained by an independent researcher via www.randomization.com. Researchers will place the generated list of random numbers in sequentially numbered opaque sealed envelopes. The consecutive participants will be randomly assigned to the treatment or placebo group at the ratio of 1:1 based on the information obtained from the envelope. Each patient who met the inclusion criteria was randomly assigned a specific number, which was consistent with the specific number of the drug formulation used. Patients in both groups were given herbal granules for treatment. The study drugs (Mudan granules and placebo) were supplied by Aoda Pharmaceutical Co., Ltd. (Liaoning, China) in the corresponding granules, which was consistent in packaging, dosage, taste, and odor. In this regard, all patients and physicians do not know the group assignment to avoid bias.

## Interventions and comparison

4

Both groups will receive routine diabetes care and treatment during the whole 8-week study. In 2011, the American Academy of Neurology published “Guidelines for the Treatment of Painful Diabetic Neuropathy” based on evidence from evidence-based medicine, which suggested that pregabalin treatment for painful diabetic neuropathy has Class A evidence. A systematic evaluation revealed that pregabalin treatment is a safe and effective treatment option for painful diabetic neuropathy in terms of suppressing pain, improving sleep therapy, and enhancing the body's tolerance.^[20–22]^ Based on all conventional treatments, including diet control, moderate exercise, stable blood glucose control, blood pressure and lipid control, and symptomatic treatment of comorbidities in both groups, except for the herbal granules, in the treatment period, the treatment regimen was divided into treatment and placebo groups according to randomization. All subjects in both groups were prohibited from using other herbal or proprietary Chinese medicines during the trial. To improve and monitor adherence, those who completed all treatments and assessments were financially compensated. In addition, each treatment form and assessment form will be completed and signed by the patients and the investigators.

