## Sample size

5

By reviewing the relevant literature,^[23]^ the independent statistician obtained the endpoint mean pain score (MPS). The mean value of the effects of the placebo group was 6.58; the standard deviation of the sample of the placebo group was 1.58; the mean value of the effects of the treatment group was 5.6; the standard deviation of the sample of the treatment group was 1.58. It is logged on the sample size calculation website (https://www.biostats.cn/statx/compute.html), and the relevant parameters were set. The 1-β test efficacy was 0.8 at *α* = 0.05 test level, the ratio of the sample size of the test group to the control group was 1:1, and 42 cases were obtained for the placebo group and the treatment group, respectively. Considering a shedding rate of no >10%, it was designed to include cases, and at least 93 patients should be included in this final clinical trial.

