### Primary safety parameter

7.1

The primary safety parameter was nerve conduction (NC) and assessed at 3 time points during the study period-baseline, endpoint, and follow-up. The mean NC measurements were compared at baseline and endpoint to determine if there were any changes in NC of nerve fibers during the study period. NC testing was carried out during follow-up to determine if any NC neurological deficits observed at endpoint were reversible 2 weeks after the end of drug treatment. All patients were required to complete the follow-up NC testing, regardless of whether they participated in this study in its entirety.

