### Secondary safety parameter

7.2

Patients’ routine blood, electrocardiogram, and liver and kidney function tests will be checked at baseline, endpoint, and follow-up of the trial, respectively, aiming to assess the safety of the treatment. All information on adverse events will be recorded at all times, including symptoms of adverse reactions, duration, severity of symptoms, management measures, etiology, and patient prognosis and regression. Investigators record, organize, analyze, and summarize in details.

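### Compensation tied to finishing the granules as well as the visits takes away a reason for early stoppers to return, and so works against the all-patient follow-up test required in Section 7.1

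*Protocol article*

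**What the plan says.** Section 4 (Interventions and comparison) of the protocol article introduces the payment with its purpose, "To improve and monitor adherence", and then gives the condition: "those who completed all treatments and assessments were financially compensated". Treatment and assessments are joined, so both have to be complete. The article gives no amount or timing, and does not say what a partial completer receives.

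Three other places bear on this:

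- Section 7.1 (Primary safety parameter): "All patients were required to complete the follow-up NC testing, regardless of whether they participated in this study in its entirety". The test is there to show whether a deficit seen at the end of treatment has reversed two weeks later.
- Section 2.2 (Ethics and registration), on patients' rights: "they could discontinue or withdraw from the study at any time during the study". Early stopping is therefore foreseen.
- Section 7.2 (Secondary safety parameter): "All information on adverse events will be recorded at all times".

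Section 2.1 sets outcome assessment before treatment and at 8 and 10 weeks. The abstract lists the visual analogue pain score and SF-36 among the outcomes. Section 5 bases the sample size on a mean pain score and allows for at most 10% loss.

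**The concern.** The payment condition mixes two things a trial needs to keep apart: taking the drug and turning up to be measured. A patient who gives up the granules in week 4 can no longer meet it, and the week 8 and week 10 visits then earn nothing under the rule. Section 7.1 nevertheless wants that patient back for nerve conduction testing, which is the primary safety parameter.

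These patients matter. Someone who stops because of a side effect, or because the pain has not eased, carries information on exactly what the trial sets out to measure. If such patients do not return, the missing values are likely to be related to tolerability or response. If that happens differently in the two arms, an analysis of those who remain no longer compares the groups as randomised.

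**Working it through.** **Step 1: what the payment rule does to each kind of patient.**

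| Patient | Meets the Section 4 condition? | Follow-up test required by Section 7.1? |
|---|---|---|
| Finishes granules, attends all visits | Yes | Yes |
| Stops granules early, attends all visits | No | Yes |
| Stops granules early, does not return | No | Yes, but not done |

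The last two rows are treated alike under Section 4. For a patient who has stopped, coming back does not change whether the condition is met. Section 7.1 depends on that patient coming back.

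**Step 2: the planned difference and sample size.** Inputs from Section 5: placebo mean 6.58, treatment mean 5.6, SD 1.58 in each group, α = 0.05, power 0.80, loss at most 10%.

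- Planned difference: 6.58 − 5.6 = 0.98.
- Normal approximation, two-sided: n = 2 × (1.96 + 0.8416)² × 1.58² / 0.98² = 40.8, so 41 per group. The noncentral t gives 42 per group (power 0.802), which is the stated figure.
- Total: 84 / 0.90 = 93.3, or 84 × 1.1 = 92.4. The stated 93 is within one patient of either.
- At 10% loss, 0.10 × 93 = 9.3, so about 9 patients in all, or 4 to 5 per arm.

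The sample size reproduces, and nothing in this point changes it.

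**Step 3: what losing early stoppers could do to the pain comparison.** Let *d* be the share of an arm whose endpoint is lost, and *g* the amount by which their pain exceeds that of completers. The mean over the whole arm is the completers' mean plus *d × g*, so completers alone understate the arm's pain by *d × g*. A completer-only difference is therefore shifted in favour of treatment by

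shift = d(Mudan) × g(Mudan) − d(placebo) × g(placebo).

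The article gives no loss by arm or by reason, so every value of *d* and *g* below is an assumption.

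| d Mudan | d placebo | g | Shift (points) |
|---|---|---|---|
| 10% | 10% | same in both arms | 0 |
| 15% | 5% | 0.5 in both | 0.05 |
| 15% | 5% | 1 in both | 0.10 |
| 15% | 5% | 1.58 in both | 0.16 |
| 15% | 5% | 2 in both | 0.20 |
| 10% | 10% | Mudan 1 to 2 points larger | 0.10 to 0.20 |

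The last row shows that equal loss rates are not enough: the reasons for loss, and so the gaps, must also match. If the imbalance runs the other way, the sign reverses.

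**Step 4: scale.** 0.10 / 0.98 = 10% and 0.20 / 0.98 = 20% of the planned difference. The standard error at 42 per arm is 1.58 × √(2/42) = 0.34, so a shift of 0.10 to 0.20 is about 0.3 to 0.6 of a standard error.

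**The case against.** The strongest reply is that one clause of a condensed article is being made to carry a great deal. Four parts of that reply deserve weight.

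- A reader might infer that non-completers receive nothing. The article does not say so. Travel costs, pro-rata payment or an exception for medical withdrawal may be set out in the full protocol or consent form, neither of which is shown. This stands. The point rests only on the condition as printed, under which an early stopper does not earn this payment.
- A reader might infer that the rule raises dropout overall. It could equally lower it, since paying for completion is meant to keep people in. This also stands: the net effect on total loss is unknown. What remains is narrower and concerns patients who stop anyway.
- A reader might infer that the rule leads patients to hide side effects. The document does not show this. Payment does not depend on being free of events, Section 7.2 has all events recorded, and blood tests, ECG and liver and kidney function are checked at set times. A patient can report an event, continue and still be paid.
- Sections 2.2, 4 and 7.1 do not contradict one another. A requirement, an incentive and a right to withdraw can coexist. That is correct; the conflict is one of incentives.

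It is also fair that Section 7.1 names only nerve conduction because that is its subject. Its silence on pain and SF-36 does not mean that these are not collected from patients who stop. None of this changes the second row of the first table in the working: the patient who stops but attends is required to come and does not earn the payment.

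**Conclusion.** The point holds as a modest weakness of design and conduct. As worded, Section 4 ties payment to drug completion as well as attendance, and so removes a reason for early stoppers to attend the follow-up that Section 7.1 requires of them.

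Bias in the treatment comparison is conditional. It needs loss rates, or reasons for loss, that differ by arm, together with an analysis that leaves out those lost. The article gives no evidence of the first and does not state the second. The payment rule is the same in both arms and patients and physicians are blinded, which makes a difference less likely but does not exclude it. A reader might take the 10% to 20% of the planned difference as the effect of the rule. It is not: it illustrates differential loss in general, and no comparison with and without the payment rule can be made from the document. Zero is within the range. The case for change rests on the low cost of protecting data from about 9 patients at the planned loss, not on a demonstrated bias.

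**What to change.** Reword Section 4 so that compensation is paid for each assessment visit attended (baseline, week 8, week 10), whether or not the patient is still taking the granules. In the same place, or in Section 7.1, state that VAS, SF-36 and adverse events are collected at those visits from patients who stopped, as Section 7.1 already requires for the nerve conduction test. If the full protocol or consent form already provides for either, a sentence in the article saying so is enough.

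The cost is small: payments to a few early stoppers and a change of wording for ethics approval. The downside is a slightly weaker financial incentive to finish the granules. No sample size, dose or clinical rule is affected.

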### Mudan granule group

4.1

We plan to use TCM granules at the beginning of treatment. All subjects will receive Mudan granules 3 times a day, 30 minutes after meals, for 8 weeks.

### Placebo group

4.2

The placebo will be provided by AODA Pharmaceutical Co., Ltd. (Liaoning, China), and the placebo group will use grain-based excipients without corresponding pharmacological effects, and the dosage precautions will be the same as those for the treatment group.

## Sample size

5

By reviewing the relevant literature,^[23]^ the independent statistician obtained the endpoint mean pain score (MPS). The mean value of the effects of the placebo group was 6.58; the standard deviation of the sample of the placebo group was 1.58; the mean value of the effects of the treatment group was 5.6; the standard deviation of the sample of the treatment group was 1.58. It is logged on the sample size calculation website (https://www.biostats.cn/statx/compute.html), and the relevant parameters were set. The 1-β test efficacy was 0.8 at *α* = 0.05 test level, the ratio of the sample size of the test group to the control group was 1:1, and 42 cases were obtained for the placebo group and the treatment group, respectively. Considering a shedding rate of no >10%, it was designed to include cases, and at least 93 patients should be included in this final clinical trial.

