## Observation indexes

6

(1) Clinical efficacy was formulated with reference to practical endocrinology and other relevant references. Apparent effects: Disappearance or significant improvement of clinical symptoms such as pain and numbness in the extremities, restoration, or significant improvement of knee and tendon reflexes, increase of nerve conduction velocity >5 m/s compared with that before treatment. Effects: The reduction of clinical symptoms such as pain and numbness in the extremities, partial restoration of knee and tendon reflexes, and the increase of nerve conduction velocity ≤5 m/s than before. In-effects: No improvement in clinical symptoms such as pain and numbness in the limbs, no improvement in knee and tendon reflexes, and no change in nerve conduction velocity. Total effective rate = (number of effective cases + number of effective cases) ÷ total number of cases × 100%.

(2) Nerve conduction velocity: NDI-092 electromyography was used for neurophysiological testing. Patients were placed in a supine position and the motor conduction velocity (MNCV) of the common peroneal nerve, median nerve, ulnar nerve and tibial nerve, and the sensory conduction velocity (SNCV) of the superficial peroneal nerve and median nerve were measured in a quiet state.

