### Statistical analysis

8.1

The data statistician of Jiangxi health vocational college of Health Professions will apply SPSS 26.0 (IBM Corp., Armonk, NY, USA) software for data processing. Furthermore, the data statisticians will use descriptive statistics to summarize the baseline situation of the 2 groups. According to the type of data information, we will use the mean and standard deviation to describe continuous variables, dichotomous variables will use the chi-squared test, and rank data will be expressed by non-parametric test. *P* < .05 has statistical significance of differences.

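### The sample size is built on a mean pain score that the outcome section does not list, and no efficacy outcome or time point is primary, so the stated 80% power and 5% error rate attach to no declared efficacy test

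*Protocol article*

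**What the plan says.** **Section 5 (Sample size).** The sizing variable comes from a cited publication: "the independent statistician obtained the endpoint mean pain score (MPS", as the section abbreviates it. The inputs are "The mean value of the effects of the placebo group was 6.58", "the mean value of the effects of the treatment group was 5.6" and an SD of 1.58 in each arm ("the standard deviation of the sample of the treatment group was 1.58" for the active arm). The operating characteristics are "The 1-β test efficacy was 0.8 at *α* = 0.05 test level". The result is 42 per arm, and 93 in total after allowing for dropout.

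**Section 6 (Observation indexes).** There are two items. The first opens "1) Clinical efficacy was formulated with reference to practical endocrinology and other relevant references" and defines a three-level grading from symptoms, reflexes and change in nerve conduction velocity, summarised as a total effective rate. The second is nerve conduction velocity itself, motor in four nerves and sensory in two. No pain score and no SF-36 appear as outcomes.

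**Abstract, Methods.** The measures observed are "visual analog scores, clinical efficacy, Medical Outcomes Study 36-item Short-Form Health Survey (SF-36) scores, nerve conduction velocity, and drug-induced adverse reactions". None is ranked.

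**Section 2.1.** Outcomes are assessed before treatment and at weeks 8 and 10. Treatment lasts 8 weeks. Neither later time is singled out for the efficacy comparison.

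**Section 7.1.** Nerve conduction is called primary, but as a safety measure. No other measure in the article is called primary.

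**Section 8.1.** One threshold, P<.05, "has statistical significance of differences". Continuous variables are to be described by mean and SD. A chi-squared test is named for dichotomous data and a non-parametric test for ranked data. No between-group test is named for a continuous variable.

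**The concern.** A power statement means something only for a particular variable, at a particular time, tested in a particular way. Section 5 gives such a statement for a mean pain score. The section that defines the outcomes contains no such score, and what it does contain has no power calculation.

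Two things are at stake. First, a reader cannot tell which comparison the 80% refers to, and so cannot tell whether a null result on the listed outcomes is informative. Second, with several efficacy measures, two post-baseline times, no primary and a single P<.05 threshold, any one significant result could be put forward as evidence that the granules work. The 5% would then be the error rate of each test and not of the efficacy claim. This cannot be repaired credibly once the data have been seen.

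**Working it through.** **1. Reproduce the plan's figure.**
Inputs from Section 5: means 6.58 and 5.6, SD 1.58 in both arms, power 0.80, alpha 0.05, allocation 1:1.
- Difference: 6.58 − 5.6 = 0.98. Standardised effect: 0.98 / 1.58 = 0.620.
- Normal approximation, two-sided: n = 2 × [1.58 × (1.960 + 0.842) / 0.98]² = 40.8, so 41 per arm.
- Two-sample t-test, two-sided: n = 41.8, so 42 per arm. Power at 42 per arm is 0.802.
- One-sided t-test: n = 32.8, so 33 per arm, which does not match.
- Dropout: 84 / 0.90 = 93.3, or 84 × 1.10 = 92.4. The stated 93 is in line with either.

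The stated 42 per arm is therefore the result for a two-sided t-test on a difference in mean pain score. Section 5 does not state the sidedness, but only the two-sided calculation gives this number.

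**2. Look for that test elsewhere in the article.**

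| Element needed | Where it should be found | What is there |
|---|---|---|
| The pain score as an outcome | Section 6 | Absent; pain enters only as an unscored part of the clinical efficacy grading |
| A link from the mean pain score to the VAS | Sections 5 and 6, abstract | None; the VAS is in the abstract and in the inclusion criteria (Section 2.3.2) |
| A primary efficacy outcome | Sections 2.1, 6 and 8.1 | None; the label is used only for nerve conduction as a safety measure (Section 7.1) |
| A time point for the efficacy claim | Sections 2.1 and 6 | Weeks 8 and 10, neither designated |
| A test for a difference in means | Section 8.1 | None named |

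**3. What a single P<.05 threshold implies if the efficacy outcomes are co-equal.**
The article does not fix the number of tests, so the counts are assumptions. Take four efficacy outcomes: VAS, clinical efficacy, SF-36 as one score, and nerve conduction velocity as one result. Count them at one time point (k = 4) or at weeks 8 and 10 (k = 8).
- Independent tests: 1 − 0.95⁴ = 0.185; 1 − 0.95⁸ = 0.337.
- With a common correlation r between the test statistics (also assumed), the chance that at least one exceeds 1.96 in absolute value is:

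| Tests | r = 0 | r = 0.3 | r = 0.5 | r = 0.7 |
|---|---|---|---|---|
| 4 | 18.5% | 17% | 16% | 13% |
| 8 | 34% | 30% | 25% | 19% |

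The independent column is an upper bound. Clinical efficacy already contains pain symptoms and nerve conduction, and weeks 8 and 10 are close together in the same patients, so positive correlation is to be expected.

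**4. After the fix.** With one primary test of the pain score, two-sided at 0.05, power at 42 per arm is the 0.802 of step 1 and the error rate of the efficacy claim is 5%, provided that SD 1.58 applies to that score.

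**The case against.** The strongest reply has four parts.

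*Pain is plainly measured.* The VAS comes first in the abstract's list and is an entry criterion, so the pain score is missing only from Section 6. This stands, and it limits the point: the defect is a mismatch between sections, not a trial that fails to measure pain. A reader might go further and infer that the mean pain score is a different instrument from the VAS, with a different SD, so that the true power is lower than 80%. The documents do not support that. The mean pain score is never defined, it could be the mean of a VAS, and the article gives no alternative SD. All that can be shown is that the two are never linked.

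*The time point is less open than it looks.* Section 7.1 separates endpoint from follow-up two weeks after treatment ends, so an endpoint pain score is compatible with week 8. That is fair, but the word in Section 5 describes a literature value, and nowhere is week 8 named for the efficacy comparison. The same section gives nerve conduction at follow-up a safety purpose, so not every week-10 test is clearly an efficacy test. That is one reason to avoid large test counts.

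*The error rates are inferred.* This also stands. A reader might count each nerve at each time separately, assume independence and arrive at a much larger figure. The article does not fix that count, and independence is implausible. Hence the range above. Even its lowest value, 13%, is more than twice 5%.

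*Multiplicity handling belongs in the analysis plan, and a journal article condenses.* This is true of the order of secondary tests and of model detail, and none of that is asked for here. It does not answer the main point: the article prints an outcome section, a sample size section and an abstract that disagree, and no unseen document can make those three agree.

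**Conclusion.** The point holds, and it should be fixed before any unblinded analysis. The variable that justifies 42 per arm is not in the outcome section, no efficacy outcome or time point is primary, and no test is named for a difference in means. The 80% power and the 5% error rate therefore attach to no declared efficacy test.

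The sample size calculation itself is not wrong. It reproduces, and it stands if a pain score with SD 1.58 is declared primary.

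If the efficacy outcomes stay co-equal at P<.05, the chance of at least one false positive is about 13-19% for four outcomes at one time point and about 19-34% for four outcomes at two. Those figures rest on assumed test counts and a common correlation from 0.7 down to 0. The finding of a mismatch between sections rests on the text alone and needs neither assumption.

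**What to change.** 1. **Section 6:** list the pain VAS and SF-36 as outcomes, with the scoring of the VAS stated.
2. **Section 6:** declare the between-group difference in the pain score at week 8, the end of treatment, the single primary efficacy endpoint.
3. **Section 6:** label clinical efficacy, nerve conduction velocity, SF-36 and all week-10 results secondary, and say that they cannot carry the efficacy claim alone. Keep the safety role of nerve conduction in Section 7.1 distinct from its role as a secondary efficacy outcome.
4. **Section 8.1:** name the between-group test for the primary endpoint, two-sided at 0.05.
5. **Section 5:** state that the sizing outcome is this pain score and that SD 1.58 applies to it. If it does not, restate the power with an SD that does.

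**Cost.** These are changes of wording, with no added patients, visits or measurements. If SD 1.58 applies, 42 per arm and 93 in total are unchanged; if not, the stated power changes. The price is that a favourable secondary result can no longer support an efficacy claim by itself.
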